### Data management

We will use the Electronic Case Reporting System with Accuracy, Safety, and Efficacy (e-CASE)—a web-based case report form (https://ecase.yuhs.ac)—for data management. The research nurse will enter data into the e-CASE, and a trained data manager will periodically check the accuracy and completeness of the entered data. The data will be kept in the archive of the data center, which has built-in security features preventing unauthorized access. Only investigators, a research nurse, and an independent monitor who will perform data monitoring and auditing will have access to the full dataset. Personal information about participants will be coded and depersonalized.

### Statistical analysis

Both intention-to-treat (considering all patients as randomized irrespective of the surveillance test they actually receive) and per-protocol analyses will be performed. The detection rate, stage distribution, and false positive rates will be compared between the noncontrast US and noncontrast MRI arms using the Fisher’s exact or chi-square test. To compare the variables between the two groups, we will use the independent t-test or Mann-Whitney U test for continuous variables and the chi-square or Fisher exact test for categorical variables. If necessary, we will perform logistic regression analysis to determine the independent associations between variables. Survival will be compared using the Kaplan-Meier methods with log-rank test. Cox proportional hazard regression will be performed to determine the independent associations between survival and potential explanatory variables.

Subgroup analyses will be performed. We will perform the analyses after excluding patients in whom liver cancer is diagnosed at their first MRI surveillance tests following the negative US prior to study enrollment. We will compare the tumor stages between patients diagnosed at the first tests and those diagnosed at later tests among patients undergoing noncontrast MRI surveillance. These analyses are intended to examine and exclude the possibility that the tumors already exist but are missed by the noncontrast US test prior to enrollment. In addition, we will examine the effects of the quality of the echogenic window to the liver and the parenchymal nodularity on our primary endpoints. Furthermore, we will explore the additional benefit of serum AFP testing in conjunction with noncontrast US or noncontrast MRI for the detection of early stage HCC. Two-sided *p*-values < 0.05 are considered statistically significant. All statistical analyses will be performed using the SAS 9.2 software package.

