### Outcomes

The primary endpoints are detection rates of very early or early stage HCC, stage distribution at the initial diagnosis, and false positive referral rates. The detection rate is defined as the number of patients whose liver cancer is detected using a given surveillance modality divided by the total number of patients under surveillance with the modality, expressed as a percentage. Very early stage cancer is defined as a single tumor < 2 cm, and early stage cancer is defined as a single tumor < 5 cm or up to three tumors < 3 cm [7, 8]. Surveillance is considered a failure when patients are diagnosed at late (i.e., intermediate or advanced) stages. The false positive rate is defined as the number of positive tests that are eventually confirmed as negative on subsequent dynamic imaging and/or pathologic examination divided by the total number of tests in a specific surveillance modality, expressed as a percentage. The secondary endpoints are 5- and 10-year overall survival rates. We will report these long-term outcomes in separate papers.

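### Stage distribution at diagnosis can be compared only among diagnosed patients, so extra small MRI tumours could look like a stage shift with no fall in late-stage cancers

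*Protocol article*

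**What the plan says.** Under Outcomes, the protocol article lists "stage distribution at the initial diagnosis" as a primary endpoint, beside the detection rate of very early or early HCC and the false positive referral rate. The detection rate has a denominator: cases found are "divided by the total number of patients under surveillance with the modality". Stage distribution is given none. The same section adds: "Surveillance is considered a failure when patients are diagnosed at late (i.e., intermediate or advanced) stages". It does not define a failure rate over the patients in an arm.

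Under Statistical analysis, the plan states: "The detection rate, stage distribution, and false positive rates will be compared between the noncontrast US and noncontrast MRI arms", and this is to be done "using the Fisher’s exact or chi-square test". Intention-to-treat analysis means "considering all patients as randomized irrespective of the surveillance test they actually receive". One sensitivity step bears on the point: "We will perform the analyses after excluding patients in whom liver cancer is diagnosed at their first MRI surveillance tests", where the ultrasound before enrolment had been negative. A second step compares stages at the first and at later tests within the MRI arm.

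**The concern.** Randomisation protects a comparison of all patients in the two arms. It does not protect a comparison of those who happen to be diagnosed, because the imaging method under study changes how many are diagnosed and with what tumours. Calling the analysis intention-to-treat does not remove this, since an undiagnosed patient has no stage to contribute.

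The late-stage share is late cancers divided by all diagnosed cancers. Extra small tumours found by MRI enlarge the denominator and leave the numerator alone. A primary endpoint could then favour MRI although as many patients as before reach a late stage, which is the event that the plan itself calls surveillance failure. A reader would take such a result as evidence that late disease had been averted.

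**Working it through.** **1. The plan's own figure, and the number of cancers it implies.** Inputs from Sample size: sensitivity 60% (ultrasound) and 90% (MRI), HCC prevalence 18% over 5 years, dropout 15%, 80% power, two-sided 5%. With the usual pooled formula for two proportions and mean 0.75:

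n = [1.960 × √(2 × 0.75 × 0.25) + 0.842 × √(0.60 × 0.40 + 0.90 × 0.10)]² / 0.30² = 31.5, or 32 cancers per arm.

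31.5 / 0.18 / 0.85 = 206 patients per arm, and 32 / 0.18 / 0.85 = 209. The stated 208 is reproduced closely. Evaluable patients per arm are 208 × 0.85 = 177, with 177 × 0.18 = 32 expected cancers. No calculation is given for the stage endpoint.

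**2. Assumed stage mix.** The article gives none. I took 9.5 very early, 9.5 early and 13 late cancers expected of 177 per arm (total 32). The MRI arm receives x additional very early tumours that do not appear in the ultrasound arm during follow-up; late cancers are equal. For scale, the assumed sensitivities differ by 32 × (0.90 − 0.60) ≈ 10 cancers per arm.

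**3. What happens to the share.** Late share among diagnosed = 13 / (32 + x). Late rate over all patients = 13 / 177.

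| Extra MRI tumours x | Late share, ultrasound | Late share, MRI | Late rate over all patients, each arm |
|---|---|---|---|
| 0 | 13/32 = 40.6% | 40.6% | 7.3% |
| 10 | 40.6% | 13/42 = 31.0% | 7.3% |
| 15 | 40.6% | 13/47 = 27.7% | 7.3% |
| 20 | 40.6% | 13/52 = 25.0% | 7.3% |

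**4. How often a test at 5% is significant.** Multinomial counts for 177 patients per arm, 40,000 simulated trials per row, Pearson chi-square without continuity correction:

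| x | Three categories, diagnosed | Early vs late, diagnosed | Late rate, all patients |
|---|---|---|---|
| 0 | 5% | 5% | 5% |
| 10 | 24% | 14% | 5% |
| 15 | 41% | 23% | 5% |
| 20 | 59% | 33% | 5% |

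With fewer late cancers (12 very early, 12 early, 8 late), x = 10, 15 and 20 gives 19%, 33% and 48% for three categories and 10%, 14% and 20% for early versus late. The late rate over all patients again stays at 5%.

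**5. The price of the alternative.** Suppose instead that totals are equal and the late share truly falls from 40% to 20% (assumed). Among 32 cancers per arm, early versus late has about 43% power. The late-stage rate over 177 patients per arm (7.2% vs 3.6%) has about 32%.

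**The case against.** - **The denominator is not written down.** This is correct, and a condensed article may leave it to the full plan. A reader might infer that the plan expressly restricts the comparison to diagnosed patients; the text does not say so. The restriction follows from the nature of the endpoint, and no failure rate over all patients is defined in its place.
- **The plan has safeguards.** The detection rate is per patient and also primary, and the investigators foresee tumours missed by ultrasound before enrolment. Both help only in part. A detection rate of early cancers cannot show that late cancers became fewer. The exclusion of cancers found at the first MRI removes patients from one arm only and leaves tumours from the later rounds, of which at least 10 in all are planned.
- **The false signal needs extra tumours in the MRI arm.** This stands. With equal totals, as the sample size assumes, a difference among the diagnosed is a real shift. The 10 to 20 extra tumours bring the MRI arm to 42/177 = 24% or 52/177 = 29% with cancer, above the planned 18%. In any one trial the effect may also fall short of significance: 13 late of 37 against 13 late of 47 gives chi-square p = 0.46.
- **The unordered test.** A reader might infer a second fault, that chi-square or Fisher wastes power by ignoring the order of stages. The documents do not support this. They give no stage mix, any gain depends on an assumed uniform shift, and order adds nothing to the early-versus-late division by which the plan defines failure. Both tests are valid for categories, and an ordered test would not cure the denominator problem.

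**Conclusion.** The point holds in a limited form. A comparison of stage among diagnosed patients cannot by itself show fewer late-stage cancers, and the plan defines no comparison over all patients that would. If MRI adds 10 to 20 very early tumours per arm with late cancers unchanged at 13 of 177, the three-category comparison is significant in about 24% to 59% of trials and the early-versus-late split in 14% to 33%, against 5% for the late-stage rate over all patients. With 8 late cancers the ranges are 19% to 48% and 10% to 20%.

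The stage mix and the number of extra tumours are my assumptions. The figures show how large the distortion could be; they do not predict that this trial will produce a false stage shift. A reader might also infer that any stage difference in favour of MRI would be an artefact, and that goes too far: if the arms yield similar cancer totals, the difference would be real.

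**What to change.** Report the rate of late-stage (intermediate or advanced) HCC per randomised patient, by allocated arm, as a risk difference with 95% CI. Count cancers from every route: scheduled imaging, AFP-triggered work-up and unscheduled examinations. Base any claim of a stage shift on this rate. Show the distribution among diagnosed patients as description, next to the total number of cancers in each arm, so that the reader can see whether the totals differ.

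The cost is a change of wording. Stage and route of diagnosis are part of the planned follow-up, and Participant flow already commits to recording unscheduled visits and examinations. The interval will be wide: with 13 late cancers of 177 in each arm, the standard error is √(2 × 0.0734 × 0.9266 / 177) = 2.8 percentage points, so the 95% CI is about ±5.4 points around zero. Power is somewhat lower than among the diagnosed (about 32% against 43% in the example above). That is the price of a comparison that randomisation protects.

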### Eligibility criteria

Eligible participants are adults aged 20–70 without history of liver cancer who are at risk of developing primary hepatic carcinoma (hepatitis B surface antigen positive [HBsAg+] or anti-hepatitis C virus positive [anti-HCV+] with cirrhosis, or cirrhosis from any causes), who have preserved liver function (Child-Pugh class A), and for whom the absence of a liver tumor has been confirmed clinically (no symptoms and no elevated tumor marker) and radiologically (on US, CT, or MRI) at the time of screening. Exclusion criteria are diagnosis of malignancy in the last 5 years, possible pregnancy, and severe cardiovascular, respiratory, renal, or infectious disease. The presence of cirrhosis will be determined based on the histologic or radiologic findings, including liver surface nodularity, margin blunting, segmental hypertrophy/atrophy, and findings secondary to portal hypertension (i.e., splenomegaly, esophageal or gastric varices, ascites, or reverse portal vein flow).

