### Sample size

Based on the past prevalence of HCC in at-risk patients undergoing surveillance in our institution, we anticipate that the prevalence of HCC in our study cohort will be approximately 18% over a study period of 5 years. The diagnostic sensitivities of noncontrast US and noncontrast MRI are expected to be 60% and 90%, respectively [10, 25]. Based on these expected prevalence and sensitivities, and an anticipated dropout rate of 15%, we calculated that we would need a sample size of 416 patients (208 for each group) to yield 80% power (1 minus the probability of a type II error) to detect a significant difference in detection rate between the noncontrast US and noncontrast MRI arms, with a two-sided type I error of 5% [32].

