### Randomization and blinding

A research nurse will assign participants into either the noncontrast US group or the noncontrast MRI surveillance group according to a computer-generated randomization list. The randomization sequence will be created using SAS 9.2 (SAS Institute, Inc., Cary, NC, USA) statistical software by an investigator with no clinical involvement in the trial, with a 1:1 allocation using a random block size of 4. Only the research nurse will have knowledge of the randomization sequence. However, once investigators obtain a participant’s consent and the research nurse assigns him or her to the noncontrast US or noncontrast MRI group, the participant and investigators will inevitably be aware of the surveillance assignment at the time of the initial surveillance examination. Therefore, blinding of participants and investigators is not possible for this trial.

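### The unadjusted primary comparison of detection rates gives up a modest amount of precision that pre-specified adjustment for baseline HCC risk could recover, and the role of the optional logistic regression is not stated

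*Protocol article*

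**What the plan says.** All references are to the protocol article.

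- **Statistical analysis:** detection rate, stage distribution and false positive rates are compared between arms by Fisher's exact or chi-square test. General two-group comparisons of variables follow, and then: "If necessary, we will perform logistic regression analysis to determine the independent associations between variables". No covariates, trigger or relation to the main test are given.
- **Randomization and blinding:** patients are allocated "with a 1:1 allocation using a random block size of 4". No stratification factor is mentioned.
- **Outcomes:** the detection rate is the number of patients whose cancer is detected by a modality, divided by all patients under surveillance with that modality.
- **Eligibility criteria:** entry is for "adults aged 20–70 without history of liver cancer" with a qualifying viral or other cause of risk, Child-Pugh class A, no elevated tumor marker, and a liver cleared by US, CT or MRI.
- **Sample size:** the planning assumption is that "the prevalence of HCC in our study cohort will be approximately 18% over a study period of 5 years". US is assumed to find 60% of cancers and MRI 90%. With 15% dropout, 80% power and two-sided 5% error, the stated size is 416 (208 per arm).

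**The concern.** Because the denominator is every patient under surveillance, an arm's detection rate depends on how many of its patients develop HCC as well as on how well the test finds them. Randomization balances HCC risk only on average, and no strata are stated to tighten that balance. Some factors plausibly related to HCC risk must be known to judge eligibility: age, cause of liver disease, a tumor marker at screening and the imaging used to clear the liver.

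An analysis that ignores them is valid but wider than it need be. The only sentence that could bring covariates in makes the model optional and does not say whether it concerns the arm comparison at all. At stake is a small amount of power on an endpoint that has little to spare, and clarity about which result is primary.

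**Working it through.** **Planned size.** Comparing sensitivities of 60% and 90% among HCC cases (two-sided 5%, 80% power, pooled variance, no continuity correction) needs 32 cases per arm. Then 32/0.18 = 177.8, and 177.8/0.85 = 209 per arm, or 418 in total. This agrees with the stated 416, so the calculation rests on sensitivities among cases.

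**The same inputs on the defined endpoint.** Taking sensitivity as the chance that a patient's cancer is detected:
- US: 0.18 × 0.60 = 10.8%. MRI: 0.18 × 0.90 = 16.2%. Difference: 5.4 points.
- Required: 628 per arm, or 628/0.85 = 739 with dropout.
- Power: about 36% at 208 per arm, and about 32% at 177 per arm (208 × 0.85).

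**Where the variance comes from** (difference in detected counts, 208 per arm):
- Total: 208 × (0.108 × 0.892 + 0.162 × 0.838) = 48.3.
- From who develops HCC: 208 × 0.18 × 0.82 × (0.60² + 0.90²) = 208 × 0.1476 × 1.17 = 35.9, or 74%.
- From detection given HCC: 208 × 0.18 × (0.60 × 0.40 + 0.90 × 0.10) = 208 × 0.18 × 0.33 = 12.4, or 26%.

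As standard errors of the risk difference:
- Whole endpoint: √[(0.108 × 0.892 + 0.162 × 0.838)/208] = 3.3 points.
- HCC-occurrence part: √[(0.1476 × 1.17)/208] = 2.9 points.

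**How much adjustment recovers.** Baseline covariates remove only the predictable part of the 74%. The document does not say how predictable HCC is in this cohort, so a range of AUCs is assumed. Simulated trials at 10.8% v 16.2% gave:

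| Adjustment | Assumed AUC | Variance reduction | Power, unadjusted → adjusted |
|---|---|---|---|
| Linear, on the true risk score, 208 per arm | 0.65 / 0.70 / 0.75 / 0.80 | 3 / 5 / 8 / 12% | 36–37% → 38.0 / 38.4 / 39.8 / 40.7% |
| Logistic, one risk score, 208 per arm | 0.66 / 0.75 / 0.81 | 3 / 7 / 14% | 36.4 → 36.9; 35.7 → 37.7; 37.6 → 42.3% |
| Logistic, one risk score, 177 per arm | 0.66 / 0.75 / 0.81 | 4 / 10 / 15% | 32.9 → 33.0; 32.4 → 34.6; 32.9 → 36.4% |
| Logistic g-computation, six fitted covariates, 208 per arm | 0.65 to 0.80 | about 1 to 11% | 36–38% → 38–41% |

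The last row is the most realistic, because it pays for estimating the coefficients.

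**Type I error** (10,000 null trials per scenario, 177 per arm):
- Unadjusted: 4.7–5.1%.
- Always adjusted: 4.8–4.9%.
- Adjusted only when a baseline test shows imbalance: 4.6–4.9%.
- Whichever of the two analyses is more significant: 5.5–6.8%.

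**Room for covariates.** Expected detected cancers are 208 × (0.108 + 0.162) = 56 with no dropout and 177 × 0.27 = 48 after dropout, so about 50.

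**The case against.** The best defence is that the primary analysis is already fixed and valid. The article names an unadjusted test, its standard error already allows for chance differences in HCC incidence, and the optional regression comes later, for associations between variables. On this view the sentence is loose wording about secondary work. Most of that stands, and it rules out several stronger readings:

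- **That chance imbalance biases the result.** It does not; the unadjusted error rate stays near 5%.
- **That the regression will adjust the arm comparison once imbalance appears, and so inflate error.** The sentence does not say so, and that rule did not inflate error. Only choosing between analyses by their results did, and the article does not provide for that.
- **That noise in HCC incidence nearly swamps the effect.** The between-arm difference in HCC incidence has a chance SD of √(2 × 208 × 0.18 × 0.82) = 7.8 patients, or 3.8 points, which looks alarming beside 5.4. But it reaches the endpoint only after multiplication by sensitivity, as 2.9 points, and the whole standard error is 3.3.
- **That the needed data are certainly in hand.** Eligibility requires these factors to be known, but the article does not say that they are captured as analysable variables.

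The defence is also right that Child-Pugh A and a non-elevated tumor marker narrow the spread of risk, which makes the upper AUCs less plausible. A covariate list and model form are commonly left to an analysis plan, so their absence is no finding. The planned work on cancers found at the first MRI, echogenic window and nodularity touches related questions, but it is described as subgroup analysis and does not adjust the main comparison.

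What the defence does not answer is that the stated test is less precise than a readily available alternative, and that the regression has no stated role.

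**Conclusion.** The point holds as a modest loss of precision and an unstated role for one model. It is not an invalid analysis. About 74% of the endpoint's variance comes from HCC occurrence. Adjustment would recover roughly 1% to 12% of the total variance for AUCs of 0.65 to 0.80, and about 15% at most in the runs at 0.81. The power gain runs from almost nothing to about 5 points, from a base of about 32% to 38%.

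These figures rest on the protocol's own 18%, 60% and 90%, and on an assumed prognostic strength that the document does not give. A reader might infer that adjustment would rescue the trial's power. It would not: with 3% to 15% less variance, the per-patient requirement falls from 739 to between 718 and 629 per arm, against 208 planned. That mismatch is a separate matter.

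**What to change.** Before outcome data are analysed, replace the optional-regression sentence with three statements:

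1. The primary detection-rate comparison is a covariate-adjusted risk difference from a logistic model with g-computation and a robust standard error. The covariates are a short fixed list of baseline factors needed for eligibility, for example age, cause of liver disease, screening AFP and pre-enrolment imaging modality, as recorded. G-computation keeps the target a difference in detection rates, so the adjusted and unadjusted results estimate the same quantity.
2. The unadjusted chi-square test is the supporting analysis.
3. Any other regression is exploratory.

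Enrollment has closed, so stratification can no longer be added, but this change still can while follow-up continues.

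The cost is wording and one more model, plus a check that the chosen factors are in the database. The list must stay short because only about 50 detected cancers are expected.

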### Participant flow

A trained research nurse will introduce the trial to potentially eligible patients, who will be provided with detailed information about the trial. They will then be able to have an informed discussion with participating physicians, who will obtain written consent if the patients agree to participate in the trial. Enrolled participants will be randomly assigned to either abdominal US or noncontrast MRI in addition to serum AFP testing for HCC surveillance (Fig. 1). They will be evaluated by at least 10 rounds of surveillance tests at 6-month intervals (with a variation of ±1 month allowed). The first surveillance test will be performed 6 months after the most recent imaging study showing no evidence of hepatic malignancy. If a new lesion detected during US or MRI surveillance is suspected to be malignant according to the predefined criteria (see Imaging evaluation section) or if the serum AFP level is elevated in an increasing trend for two consecutive tests, dynamic contrast-enhanced CT will be performed [6, 30]. The reference value for AFP is less than 9 ng/mL at our institution. Additional dynamic liver MRI may be performed at the discretion of clinicians. If the surveillance test result is determined to be a false positive by subsequent tests, the patient will return for the next scheduled surveillance test. If a patient is confirmed as having a hepatic malignancy, the patient will receive standard treatment according to the guidelines [5–8]. We will continue follow-up of treated patients for at least 5 years to obtain and compare the overall survival rates.

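### The supporting analysis for tumours missed before enrolment drops first-round cancers from the MRI arm only, which biases its detection-rate comparison against MRI

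*Protocol article*

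**What the plan says.** All points are in the protocol article.

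- **Main analyses** (Statistical analysis): "Both intention-to-treat (considering all patients as randomized irrespective of the surveillance test they actually receive) and per-protocol analyses will be performed". They cover detection rate, stage distribution and false positive rate.
- **Exclusion** (same section, introduced as a subgroup analysis): the analyses are repeated after "excluding patients in whom liver cancer is diagnosed at their first MRI surveillance tests following the negative US prior to study enrollment". No corresponding rule is given for cancers found at the first US test.
- **Companion analysis**: "We will compare the tumor stages between patients diagnosed at the first tests and those diagnosed at later tests among patients undergoing noncontrast MRI surveillance".
- **Purpose**: "These analyses are intended to examine and exclude the possibility that the tumors already exist but are missed by the noncontrast US test prior to" (the sentence closes by naming study entry).
- **Detection rate** (Outcomes): "the number of patients whose liver cancer is detected using a given surveillance modality divided by the total number of patients under surveillance with the" (that is, the same imaging test).
- **Entry conditions, the same for both arms**: absence of tumour is confirmed "radiologically (on US, CT, or MRI) at the time of screening" (Eligibility criteria), and "The first surveillance test will be performed 6 months after the most recent imaging study showing no evidence of hepatic malignancy" (Participant flow).

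**The concern.** The exclusion is defined by something that happens after randomisation, a cancer diagnosis at round 1, and it is applied in one arm. Both arms enter after the same kind of negative imaging, wait the same six months and are allocated 1:1. On average they therefore carry the same number of tumours that the earlier imaging missed. First-round US will find some of these, and they stay in the US count. The corresponding MRI cases are removed. Because six months have passed, the rule also removes MRI cancers that arose after the negative US, which are not its target.

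The purpose is to learn whether an apparent MRI advantage merely reflects tumours already present at entry. A rule that lowers the MRI detection rate whenever any cancer is found at a first MRI test will shrink the difference whether or not that explanation is true. A trial with a real MRI benefit could then be reported as showing mainly a first-round effect.

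**Working it through.** **Inputs from the protocol article.** HCC prevalence 18% over 5 years, sensitivities of 60% (US) and 90% (MRI), dropout 15%, 208 patients per group (Sample size); at least 10 rounds (Participant flow).

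**Check of the inputs against the planned size.** Comparing 60% with 90% among cancer cases (80% power, two-sided 5%) needs 31.5 cases per arm, rounded up to 32.
- Unrounded: 31.5 / 0.18 = 175, and 175 / 0.85 = 206 per arm.
- Rounded up at each step: 32 / 0.18 = 178, and 178 / 0.85 = 210 per arm.

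These bracket the stated 208, so the inputs are read as intended. The exclusion itself carries no stated figure to reproduce.

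**Design detection rates.** US 0.18 × 0.60 = 10.8%; MRI 0.18 × 0.90 = 16.2%; difference 5.4 points. Evaluable patients per arm: 208 × 0.85 ≈ 177. Expected detected cancers: US 177 × 0.108 = 19.1; MRI 177 × 0.162 = 28.7.

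**Assumption.** The round-1 share *s* of detected cancers is not in the documents. An even spread over 10 rounds gives 10%; a larger first-round yield is represented by 20% and 30%.

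**Formula.** With D cancers detected among N patients, removing the round-1 cases from numerator and denominator gives (D − sD) / (N − sD).

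Example, MRI at design rate, s = 10%: (28.67 − 2.87) / (177 − 2.87) = 14.8%. Against an untouched US rate of 10.8% the difference is 4.0 points. Excluding in US as well gives (19.12 − 1.91) / (177 − 1.91) = 9.8%, a difference of 5.0 points.

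MRI minus US, in percentage points:

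| Round-1 share | Equal detection (10.8% each): MRI-only rule | Equal detection: both arms | Design rates: MRI-only rule | Design rates: both arms |
|---|---|---|---|---|
| No exclusion | 0.0 | 0.0 | 5.4 | 5.4 |
| 10% | −1.0 | 0.0 | 4.0 | 5.0 |
| 20% | −2.0 | 0.0 | 2.6 | 4.6 |
| 30% | −3.0 | 0.0 | 1.1 | 4.1 |

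**Break-even at the design rates.** The MRI-only difference reaches zero when the number removed is (0.054 × 177) / (1 − 0.108) = 9.56 / 0.892 = 10.7, which is 37% of the 28.7 MRI-detected cancers.

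**Second model, in which missed tumours carry over to the next round.** Assume 18% / 10 = 1.8% new tumours per round, so 3.74 per arm of 208. Assume also that all earlier imaging was US at 60%, leaving a backlog of 3.74 × 0.4 / 0.6 = 2.50 missed tumours at entry.
- Round-1 detections: MRI 0.9 × 6.24 = 5.62; US 0.6 × 6.24 = 3.74.
- Over 10 rounds: MRI 39.52 / 208 = 19.0%; US 37.44 / 208 = 18.0%; difference 1.0 point.
- MRI-only rule: (39.52 − 5.62) / (208 − 5.62) = 16.8%, which is 1.2 points *below* US.
- Both arms: US becomes (37.44 − 3.74) / (208 − 3.74) = 16.5%, leaving MRI about 0.3 points ahead.

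Here the one-arm rule reverses the sign. The two-arm rule keeps it but does not recover the full difference.

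**The case against.** The strongest defence has four parts.

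1. **It is a supporting analysis.** The exclusion is listed after the intention-to-treat and per-protocol analyses and replaces neither. This stands. A reader might infer that the trial's randomised comparison is broken; the documents do not support that.

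2. **It can be read as deliberately conservative.** Deleting all first-round MRI cancers while leaving the US count whole is a worst case for MRI. If MRI still leads, first-round detection of pre-existing tumours cannot explain the detection-rate advantage. This also stands, so it would be too strong to say that the analysis can tell us nothing. But the article does not describe it as a bound, and its stated aim is to examine the explanation as well as to exclude it. When the advantage disappears, the result has no clear reading.

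3. **The asymmetry has a reason.** For patients last imaged by US, only the MRI arm changes modality, so a catch-up yield is expected there. That explains the interest in round-1 MRI cases. It does not justify removing all of them, including the share that US would also have found and tumours that arose after the negative US.

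4. **A two-arm exclusion is not clean either.** It still selects on a round-1 result, and US may leave more entry tumours to be found and credited in later rounds. This stands, as the second model shows, and it limits what the corrected analysis can claim.

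It might also be argued that only a description within the MRI arm was meant. The wording more naturally refers to the between-arm analyses set out just before; if a description was meant, the sentence needs to say so. The first-versus-later stage comparison within the MRI arm is descriptive and fits its purpose; it is not an error.

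**Conclusion.** The concern holds for this supporting analysis and for detection rate. The direction is certain: any cancer removed from the MRI arm alone lowers the MRI rate relative to US. The size depends on the round-1 share, which the documents do not give. For shares of 10% to 30%, with equal true detection of 10.8%, the rule produces a false MRI deficit of about 1 to 3 points. At the design rates it reduces 5.4 points to 4.0 to 1.1, against 5.0 to 4.1 with the exclusion in both arms. Other assumptions change these figures, and in the carry-over model the sign reverses.

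A reader might extend the bias to all three primary endpoints. That is not supported: for stage distribution the direction depends on which tumours are removed, and false positive rates are hardly affected. The intention-to-treat and per-protocol results do not change. The practical consequence is one of interpretation: an MRI advantage that survives the rule is informative as a worst-case bound, while one that is lost under it cannot be attributed to tumours present at entry. The point is moderate and worth correcting before the endpoint analysis.

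**What to change.** - **Apply the exclusion to both arms.** Drop every patient, in either arm, whose cancer is diagnosed at or before the first surveillance test. Use the same prior-imaging condition in both arms; the present rule names only a negative US, whereas eligibility also allows CT or MRI.
- **Label it exploratory**, stating that it conditions on a post-randomisation result and that US may leave more entry tumours for later rounds.
- **Add a comparison of the arms stratified by pre-enrolment imaging modality** (US versus CT or MRI). This is a baseline variable, so it keeps the randomised comparison intact.
- **If the MRI-only version is kept**, describe it as a worst-case bound for MRI and say that only a surviving advantage will be interpreted.

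Reporting the first-versus-later stage comparison in the US arm too would be a useful optional addition.

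The cost is small: one reworded supporting analysis with slightly fewer events, and one added stratified comparison, with no new trial procedures. The article reports that follow-up for the endpoints was still ongoing.
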